## Abstract

**Background:**

Aging leads to a decline in muscle mass and strength, contributing to frailty and decreased quality of life. Sirolimus (rapamycin) , an mTOR inhibitor, has shown potential in preclinical studies to extend lifespan and improve health span. This study evaluates the safety and efficacy of once-weekly sirolimus (rapamycin) administration on muscle strength and endurance in older adults engaged in a 13-week exercise program.

**Methods:**

This randomized, double-blind, placebo-controlled trial will enroll 40 participants aged 65–85. Participants will be randomly assigned to receive either sirolimus (rapamycin) 6 mg/week or placebo for 13 weeks, in conjunction with an at-home exercise program. The primary outcome measure is the change in muscle strength and endurance, assessed by the 30-Second Chair-Stand Test. Secondary outcome measures include adverse events, changes in muscle strength and endurance as measured by the 6-min walk test, handgrip strength, and participant-reported outcomes using the SF-36 survey. Assessments will be conducted at baseline, mid-intervention (week 6), and post-intervention (week 13). Blood samples will be collected for hematology and biochemistry analyses, including full blood count, urea and electrolytes, liver function tests, HbA1c, lipids, serum IGF-1, and hs-CRP. DNA methylation will be analyzed using TruDiagnostic™ to explore changes in biological age.

**Discussion:**

This study aims to provide insights into the potential benefits of intermittent sirolimus (rapamycin) administration on muscle performance in older adults. By alternating periods of mTOR inhibition through rapamycin and activation via exercise, this study will explore a novel approach to enhancing muscle strength and endurance in the aging population. The results could have significant implications for developing interventions to improve physical function and overall health outcomes in older adults. Safety and tolerability will also be closely monitored to ensure the feasibility of this regimen for wider application.

**Trial registration:**

Australia New Zealand Clinical Trials Registry, ACTRN12624000790549. Registered on 26 June 2024 https://www.anzctr.org.au/Trial/Registration/TrialReview.aspx?ACTRN=12624000790549.

## Administrative information

Note: the numbers in curly brackets in this protocol refer to SPIRIT checklist item numbers. The order of the items has been modified to group similar items (see http://www.equator-network.org/reporting-guidelines/spirit-2013-statement-defining-standard-protocol-items-for-clinical-trials/).

## Introduction

### Background and rationale {6a}

#### Brief mechanistic hypothesis

Periods of time where the mechanistic target of rapamycin (mTOR) pathway is activated via exercise, combined with alternate periods of time where mTOR is inhibited using rapamycin (sirolimus), will result in greater muscle performance in older adults compared with just exercise alone. 

#### Background

Human skeletal muscle undergoes significant changes with aging, characterized by a decline in muscle mass and strength at an approximate rate of 1% per year starting around the age of 40 [1]. This decline in strength is inversely associated with all-cause and cardiovascular mortality [1]. Muscle wasting contributes to weakness, disability, increased hospitalization, immobility, and loss of independence. Interventions for sarcopenia, including exercise and nutrition, positively impact protein anabolism and enhance physical function, quality of life, and an anti-inflammatory state in older adults [1].

#### Sirolimus (rapamycin)

Sirolimus (rapamycin), also known as Rapamune, is a natural macrocyclic lactone produced by the bacterium *Streptomyces hygroscopicus*. It is FDA-approved for conditions like immunosuppression to prevent organ transplant rejection and inhibition of vascular smooth muscle cell proliferation in drug-eluting coronary stents. It is also used in treating various cancers and lymphangioleiomyomatosis due to its antiproliferative effects [2].

#### Mechanistic target of rapamycin (mTOR)

mTOR is a protein kinase belonging to the phosphoinositide 3-kinase (PI3K)-related kinase family, forming two types of multiprotein complexes: mTORC1 and mTORC2 [3, 4]. Both complexes play vital roles in cellular regulation, and their dysregulation disrupts cell homeostasis, potentially leading to aging-related pathologies. Sirolimus (rapamycin) is a specific allosteric inhibitor of mTORC1, which plays critical roles in regulating mRNA translation, promoting lipid and nucleotide synthesis, and repressing catabolism and autophagy [5]. mTORC1 is highly sensitive to sirolimus (rapamycin), while mTORC2 is only inhibited after prolonged exposure [5].

#### Preclinical evidence

There is abundant preclinical evidence that mTORC1 activity is a major driver of the biological aging process. In multiple organisms, genetic or pharmacological inhibition of the mTORC1 pathway has been shown to extend life and broadly delay molecular and functional declines associated with aging. These include genetic studies demonstrating that depleting mTOR or Raptor (a subunit of mTORC1) has life-extending effects in yeast [6], nematodes [7, 8], flies [9], and mammals [10], and similar outcomes when each of these organisms are treated with sirolimus.Mouse: sirolimus (rapamycin) treatment increases median and maximum lifespan when started at middle age (270 of 600 days of age) [11]. Treatment for only 3 months at middle age was sufficient to increase life expectancy by up to 60% and improve measures of health span in middle-aged mice [12]. Furthermore, sirolimus (rapamycin) treatment in mice was shown to increase alveolar bone levels [13], improve cardiovascular function [14–16], decrease body weight [17], and remodel the microbiome [12].Rat: sirolimus (rapamycin) treatment reduces food intake and body weight [16], increases grip strength, and attenuates the decline in maximum running distance [18]. Daily dosing in food did cause some diabetes-like symptoms [18], but repeated low doses do not seem to influence glucose homeostasis with long-term use [16].Dog: a study by Urfer et al. showed that low-dose (0.05 mg/kg and 0.10mg/kg) sirolimus (rapamycin) treatment three times a week over a period of 10 weeks in middle-aged dogs was well tolerated, with no clear adverse effects except for a decrease in the volume of red blood cells. The dogs had improvements in their left ventricular cardiac function and had increased activity [19].

#### Clinical evidence

FDA-approved uses: sirolimus is approved for immunosuppression in organ transplant patients and cancer treatment, with higher doses associated with significant side effects including stomatitis, diarrhea, nausea, anemia, cytopenia, hyperglycemia, and hyperlipidemia, as well as the (intended) immunosuppressive effect.Low-dose studies: lower doses of sirolimus have shown safety in older populations. Studies have demonstrated well-tolerated doses with few mild side effects and improved immune function in elderly subjects [20–25].Exercise interaction: a study in young males found that sirolimus taken before resistance exercise impaired mTORC1 signaling and muscle protein synthesis, indicating the importance of timing sirolimus administration on non-exercise days [26].

#### Selection of orally bioavailable rapamycin analogue

Although structurally similar, sirolimus and everolimus do not have identical effects on the mTOR pathway. Sirolimus primarily inhibits mTORC1, whereas everolimus is more effective at inhibiting mTORC2 at clinically relevant concentrations [27]. Life span-enhancing effects of mTOR inhibitors seen in preclinical models are predominantly linked to mTORC1 inhibition, while inhibiting mTORC2 might be detrimental, as mTORC2 controls insulin-mediated suppression of hepatic gluconeogenesis [28]. Therefore, sirolimus has been selected for this study as it preferentially inhibits mTORC1 without significantly affecting mTORC2.

#### Rationale

Sirolimus (rapamycin) has the potential to restore mTORC1 balance by inhibiting its overactivation, which is commonly seen in aged muscles [29]. While mTORC1 is typically activated by branch-chain amino acids like leucine or by anabolic stimuli such as exercise, its chronic activation in older muscles leads to muscle atrophy rather than protein synthesis [29]. This atrophy is primarily due to the suppression of autophagy, highlighting the importance of mTORC1-regulated autophagy in aging muscle [29].

Weekly dosing with sirolimus (rapamycin) may provide alternating periods of mTORC1 activation (promoting protein synthesis) and inhibition (inducing autophagy), thereby improving muscle health. Given sirolimus (rapamycin)’s long half-life of 64 h in humans, weekly administration should be sufficient to create these beneficial cycles.

Combining exercise with weekly sirolimus dosing may offer synergistic benefits, enhancing muscle performance more effectively than exercise alone. This study aims to utilize a low-dose sirolimus protocol to balance therapeutic mTORC1 inhibition with minimal side effects, potentially offering a safe and effective strategy to boost muscle strength and endurance in the aging population.

## Objectives {7}

### Primary objective

The primary objective of this study is to evaluate the effect of once-weekly sirolimus (rapamycin) 6 mg on muscle strength and endurance in an older population engaged in a 13-week exercise program, compared to the exercise regimen alone. This evaluation will be primarily conducted through the 30-Second Chair-Stand Test (30CST), a measure specifically chosen for its relevance and sensitivity in assessing functional muscle performance in the elderly. The study seeks to establish that the addition of sirolimus (rapamycin), an inhibitor of the mechanistic target of rapamycin (mTORC1) pathway, does not adversely affect the exercise-induced improvements in muscle performance. Additionally, this study seeks to provide initial insights into whether intermittent modulation of mTORC1 signaling through this combined approach could enhance muscle performance beyond what is observed with exercise alone in older adults.

### Secondary objectives

There are several secondary objectives of this study as outlined below:To investigate the safety and tolerability of low-dose rapamycin in exercising older adults.

Safety and tolerability measures utilized to investigate the incidence, relatedness, seriousness, and severity of adverse events include:Clinical laboratory tests (full blood count, U&Es, LFTs, HbA1c, lipids, serum IGF-1)Vital sign measurementsAdverse events, serious adverse events, and events that impact exercise ability or dosing.

2.To evaluate change of muscle strength and muscle endurance from baseline to EOS Muscle strength and endurance measures will be evaluated by evaluating change from baseline in the:30-Second Chair-Stand Test (30CST)6-min walk testHandgrip strength

We will assess changes in upper body strength and cardiovascular endurance using grip strength and the 6-min walking test, respectively. The grip strength test will provide valuable insights into the impact of the intervention on muscular strength and function, critical for daily activities and autonomy in the elderly. The 6-min walking test will evaluate alterations in aerobic capacity and endurance, indicative of the participants’ ability to perform sustained physical activities.3.Participant-reported outcomesChange from baseline in the self-reported measures of health status and quality of life as determined by the 36-Item Short Form Survey (SF-36) through EOS.

The validated SF-36 tool provides measurement of the intervention’s impact from the participants’ perspective, encompassing aspects such as pain, general health perceptions, physical functioning, emotional well-being, and social functioning.

Participant self-reported physical activity, from baseline to EOS via participant diary.

#### Exploratory objectives

Additional exploratory objectives of this study are to investigate the potential effects of the combined exercise regimen and rapamycin treatment on biological aging markers and systemic inflammation, which are key factors in the aging process.Epigenetic age assessment

Utilizing the advanced methodology of epigenetic clocks based on DNA methylation status, this study aims to explore the intervention’s impact on biological age.2.Inflammation and aging (inflamm-aging)

Chronic inflammation is a recognized hallmark of aging, and managing the balance between pro-inflammatory and anti-inflammatory signals is crucial for healthy aging. By examining changes in hs-CRP, we aim to explore how the intervention influences systemic inflammation, thereby contributing to our understanding of the mechanisms underlying aging and longevity.

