#### Epigenetic clocks

Epigenetic clocks are based on the methylation status of a set of genomic positions and provide an accurate age estimate in humans. Samples can be obtained from various cell types, including white blood cells, cheek cells obtained via a cheek swab, brain, the colon, and other organs (hence, it is considered a biomarker for the age of almost every part of the body). This sets the method apart from tests that rely on biomarkers of age that work in only one or two tissues, including the gold-standard dating procedure, aspartic acid racemization, which analyses proteins that are locked away for a lifetime in tooth or bone. In human DNA, methyl groups most often attach at CpG sites, where a cytosine precedes a guanine in the DNA. This process is catalyzed by at least three DNA methyltransferase (DNMTs). A typical human genome contains more than 28 million such sites. For this study, a genome-wide assessment of DNA methylation will be performed by TruDiagnostics via blood and saliva samples.

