### DNA methylation

At baseline (visit 2) and end of study (visit 4), all participants will provide a sample of whole blood to conduct DNA methylation testing with TruDiagnostic™, based in the United States of America (USA). Samples may be taken separately by finger-prick lancet onto the provided blood spot card, or whole blood can be taken from a no-additive sample tube already taken from the participant by venipuncture at the time. Preparation of the blood spot card will be according to the instructions provided by TruDiagnostic™. Collected samples will be stored at the site, at room temperature, and sent in batches to the TruDiagnostic™, no less than every 8 weeks to ensure that samples are viable when arriving at the analysis laboratory in the USA. Samples will be destroyed following analysis. Individual results will not be provided to participants as samples will be deidentified. If blood samples are lost or damaged and cannot be shipped for analysis, participants will be asked to provide another sample if the sample was lost within a week of providing the initial sample.

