### Statistical methods

#### Statistical methods for primary and secondary outcomes {20a}

As some of the feasibility issues are related to the efficacy analyses, they are described first. The efficacy analysis plan is intended to match the analysis plan of the full trial closely.

Efficacy analysisAnalysis sets◦ Intention-to-treat (ITT) analysis set: This set will be used for the primary analysis and will include all randomized participants in their originally assigned groups.◦ Per-protocol (PP) analysis set: this set will be used for sensitivity analyses and will include participants who complete at least 75% of the exercise sessions and take at least 75% of the protocol-stipulated doses of sirolimus (rapamycin) or placebo.General inferential analysis plan◦ Outcomes at 13 weeks will be analyzed using regression models, adjusting for baseline values of the outcomes. Generalized linear models (GLM) will be employed, selected during a blind review of the data without knowledge of group allocation.◦ Final analyses will utilize the selected GLMs, and parametric assumptions will be addressed using the wild bootstrap method to estimate standard errors [35, 36]. For larger trials, standard sandwich estimators of the variance would be used in lieu of the bootstrap.Handling missing data◦ Multiple imputations will be used to create 15 completed datasets. The nominal significance level for this phase 2a study will be set at 0.1; however, in line with current thinking regarding preliminary studies, the results will deemphasize testing and emphasize point and interval estimation, producing confidence intervals for active arm effect having between 75% and 95% confidence levels in increments of 5 percentage points [27].Sensitivity analyses◦ Sensitivity analyses will be performed on the per-protocol analysis set and the complete-data-only set, excluding cases with missing data.

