### Methods for additional analyses (e.g., subgroup analyses) {20b}

Subgroup analyses: subgroup analyses will be conducted to explore the potential differential effects of the intervention across various participant characteristics and to provide a more detailed understanding of the efficacy and safety of sirolimus (rapamycin) in conjunction with exercise. These additional analyses are not limited to the following:Age groups: participants will be stratified into age groups (65–74 and 75–85 years) to assess whether the intervention’s effectiveness varies with age.Gender: the impact of the intervention will be evaluated separately for male and female participants to identify any gender-specific effects.Baseline fitness levels: participants will be grouped based on their baseline fitness levels, as measured by the 30-Second Chair-Stand Test (30CST) and other baseline assessments, to determine if initial fitness influences the intervention’s outcomes.Adherence to protocol: Subgroup analyses will consider adherence levels, comparing outcomes between participants who adhered strictly to the exercise and medication regimen (≥75% adherence) and those with lower adherence.

Adjusted analyses: adjusted analyses will be performed to account for potential confounding factors and to provide a more accurate estimate of the intervention's effects.Baseline covariates: the primary and secondary outcome analyses will be adjusted for relevant baseline covariates, such as age, gender, baseline fitness levels, and any other significant factors identified during the blind review of the data.Generalized linear models (GLM): these models will be used to account for repeated measures and the correlation between baseline and follow-up assessments.

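### Biological age is read from whole blood and the stated models adjust only for baseline variables, so a drug-related shift in white-cell mix could not be told apart from a change in biological age

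*Protocol article*

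**What the plan says.** Under Exploratory objectives, the epigenetic aim reads "Utilizing the advanced methodology of epigenetic clocks based on DNA methylation status, this study aims to explore" the effect of the intervention on biological age.

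On the sample, the DNA methylation section states that "all participants will provide a sample of whole blood to conduct DNA methylation testing", at Visits 2 and 4, and the section on biological specimens {33} agrees. The Epigenetic clocks section, which stands under Secondary outcomes, instead says that a "genome-wide assessment of DNA methylation will be performed by TruDiagnostics via blood and saliva samples".

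On the analysis, section {20a} gives the general rule: "Outcomes at 13 weeks will be analyzed using regression models, adjusting for baseline values of the outcomes". Section {20b} adds, under the label of baseline covariates, that "the primary and secondary outcome analyses will be adjusted for relevant baseline covariates, such as age, gender, baseline fitness levels, and any other significant factors" found at blind review will be used.

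On the drug, the Clinical evidence section describes "higher doses associated with significant side effects including stomatitis, diarrhea, nausea, anemia, cytopenia, hyperglycemia, and hyperlipidemia", together with an intended immunosuppressive effect. For lower doses in older people it reports "well-tolerated doses with few mild side effects and improved immune function in elderly subjects". Under Preclinical evidence, the low-dose dog study found "no clear adverse effects except for a decrease in the volume of red blood cells".

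A full blood count is scheduled at Visits 1, 3 and 4. No section links it to the methylation analysis.

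**The concern.** A methylation value from whole blood is an average over the white cells in the sample. If cell types differ in methylation, the average moves when their proportions move, even if no cell has aged differently. If sirolimus changes those proportions, the change arises after randomisation and in one arm. Randomisation does not balance it, and adjusting for baseline variables does not remove it.

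What is at stake is the interpretation of the result. An arm difference in the clock reading could reflect a change within cells, a change in cell mix, or both, and the analysis as described offers no way to judge which. The exploratory aim is worded in terms of biological age, so the distinction affects what the trial may say.

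**Working it through.** The plan states no figure on this point, so the check is a comparison of passages followed by an illustration on assumed inputs.

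**Step 1: what the models adjust for.** Section {20a} adjusts for the baseline value of the outcome. Section {20b} adds age, gender, baseline fitness and factors from blind review, all as baseline covariates, for primary and secondary outcomes. The clock is exploratory in the objectives but listed under Secondary outcomes later, so it is unclear whether {20b} applies to it. Either way, no term for cell composition at follow-up is named.

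**Step 2: what the protocol says about blood cells.** Cytopenia and immunosuppression are tied to higher doses. For lower doses the text speaks of better immune function, and the dog finding concerns red cells. Immune action is thus described at both dose levels, but no passage reports a change in white-cell mix at any dose.

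**Step 3: what data exist.** The methylation samples are taken at Day 0 and Day 91 (+7). Full blood counts are taken at screening (Day -28 to -1) and at Visit 4. The baseline count therefore precedes the baseline methylation sample by 1 to 28 days, while the end-of-study count falls at the same visit. The exclusion criteria use both a white-cell count and an absolute neutrophil count, so a neutrophil proportion can be formed at screening.

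**Step 4: illustration in SD units.** These inputs are assumptions and are not in the documents:
- arm difference in cell-mix change: 0.25, 0.5 or 0.8 SD
- correlation *r* between clock change and cell-mix change: 0.3, 0.5 or 0.7
- no change within cells

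From the Sample size section come 20 per arm and a nominal level of 0.1, taken here as two-sided. Displacement of the clock contrast = shift × *r*. The chance of rejection follows from the noncentral t distribution with 38 degrees of freedom and noncentrality displacement × √(20/2).

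| Shift (SD) | r = 0.3 | r = 0.5 | r = 0.7 |
|---|---|---|---|
| 0.25 | 0.075 SD; 0.109 | 0.125 SD; 0.125 | 0.175 SD; 0.150 |
| 0.5 | 0.15 SD; 0.137 | 0.25 SD; 0.200 | 0.35 SD; 0.292 |
| 0.8 | 0.24 SD; 0.193 | 0.40 SD; 0.346 | 0.56 SD; 0.538 |

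Each cell gives the displacement and then the chance of rejection, against 0.10 nominal. These rejections are misleading only if they are read as evidence of a change in biological age. As statements about the total effect on the clock reading they are correct.

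**Step 5: illustration in years.** Assume that clock readings differ by 2 to 10 years between white-cell types (not in the documents). Displacement = difference × shift in proportion.
- 5-point shift: 2 × 0.05 = 0.10 to 10 × 0.05 = 0.50 year
- 10-point shift: 2 × 0.10 = 0.20 to 10 × 0.10 = 1.0 year

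For scale, 91/365.25 = 0.249 year of calendar time passes between the samples. This is a yardstick only if the clock reports years and advances one-for-one with time. It is not a ceiling on a real effect, since a reading could also fall.

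**The case against.** The strongest reply is that this is a detail for the analysis plan. The outcome is exploratory, section {20a} is a general plan with model choice left to blind review, and a protocol article need not name every covariate. That stands in part: the absence of a cell-composition term is not in itself an error. What remains is that the article does state its adjustments, and all of them are baseline variables, which cannot address an on-treatment shift.

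A second reply is that the randomised comparison validly estimates the total effect of the drug on the clock reading, by whatever route. This stands in full, and it is why the planned analysis should remain the main one.

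A third reply is that the mechanism and the numbers are assumed. This also stands. The protocol does not say that white-cell types give different readings, it presents the clock as usable across cell types, and it names no particular clock.

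A reader might infer something stronger: that the protocol itself says the trial dose alters white-cell counts, that the epigenetic result will therefore be biased, or that the exploratory aim cannot be answered. The documents do not support this. Cytopenia is stated for higher doses only, the low-dose blood finding concerns red cells in dogs, the white-cell thresholds are entry criteria and not on-treatment findings, and the aim is only to explore.

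**Conclusion.** The point holds as a risk to interpretation. The clock is read from whole blood, the drug is described as acting on the immune system, and the stated models contain only baseline terms. If cell mix shifts on treatment, its contribution to the clock contrast cannot be separated from a change in biological age.

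The size is unknown. The illustrated displacements run from 0.075 to 0.56 SD, or from 0.10 to 1.0 year, and depend wholly on assumed values for the shift and for the clock's sensitivity to it. The primary outcome is unaffected. This is a cheap improvement to an exploratory analysis and not a defect that invalidates it.

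The conflict between whole blood in one section and blood and saliva in another is a separate, factual inconsistency about the same outcome.

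**What to change.** 1. Keep the planned baseline-adjusted comparison as the main estimate of the total effect on the clock reading.
2. Report beside it a sensitivity analysis that adds white-cell proportions at both visits. Preferably estimate these from the same methylation samples, if the laboratory reports them. Otherwise use the full blood counts at Visits 1 and 4, and note that the screening count may precede the Visit 2 sample by up to 28 days.
3. If the two results differ, state that the clock effect may run partly through blood-cell composition. Do not make the adjusted model decisive: with about 20 per arm, a weaker adjusted result may reflect mediation or lost precision.
4. Reconcile the Epigenetic clocks section with the DNA methylation and specimen sections on whether saliva is collected.

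The cost is one extra regression, with no new visit or sample. One cell proportion entered as a change uses one degree of freedom; entered at both visits it uses two. With 40 participants and a model containing an intercept, arm and baseline value, residual degrees of freedom fall from 37 to 36 or 35. The main downside is that the added model conditions on a post-randomisation variable that may be a mediator, so it can only be read alongside the planned result.
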